### Primary outcome

2.8

The primary outcome is SDLP (in centimeters), which is the distance from the center line of the road to the right end of the car body in the road tracking test. SDLP in the road tracking task known to be a more sensitive index than other variables,^[18]^ and its validity and reliability have been confirmed.^[5,11,19]^ Since SDLP has been used as a primary evaluation item to assess the influence of drugs on driving performance, it was also set as the main evaluation item in the present DS study.

### Secondary outcomes

2.9

The following secondary DS outcomes will be used: total number of times the car body crosses the lane (inappropriate line crossing; ILC); total number of times the vehicle goes off of the course (course-outs); standard deviation of speed in the road tracking test; reaction time for detecting deceleration of the preceding vehicle (time to speed adaptation); number of collisions with the preceding vehicle (car collisions) in the car following test; brake reaction time (BRT); and number of collisions with an object (error) in the harsh braking test.

### Other outcomes

2.10

In addition to the DS evaluation, the following items will also be evaluated. Considering the possibilities of DS sickness and drowsiness at the time of the examination and alcohol-induced mood changes affecting the results, the Japanese version of the KSS,^[20]^ Japanese version of the POMS 2,^[21]^ and SSQ^[22]^ will be conducted simultaneously.

### Statistical analysis

2.11

For the statistical analysis, we will calculate the basic statistics of accumulated SDLP through 60 minutes for each BAC and the difference from BAC 0%. The predicted difference in SDLP between the BAC 0.05% and 0% groups will be calculated using a linear model. Basic statistics for the secondary outcomes will also be calculated. Evaluation items with incomplete data will be excluded from analysis, and outliers will be treated as missing values.

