Therefore, with the aim of establishing such an evaluation system, we planned a validation study using a DS and alcohol that would meet legal standards around the world. The purpose of this study targeting healthy adult males is to set a clinically meaningful SDLP threshold as a main evaluation item based on the difference between SDLP at blood alcohol concentration (BAC) levels of 0.00% and 0.05%. We set the SDLP threshold with a BAC of 0.05% as the impaired level. The upper limit of BAC set by law ranges from 0% to 0.08% from country to country.^[7]^ However, the International Council on Alcohol, Drugs, and Traffic Safety^[8]^ reported a BAC <0.05% is relatively safe, a BAC of 0.05% to 0.08% induces mild to moderate side effects, and a BAC of ≥0.08% poses a potentially dangerous risk. In fact, in most countries, a BAC of 0.05% is set as the upper limit. Although some reports have shown that cooperative muscle movement is impaired starting at a BAC of 0.035%,^[9]^ epidemiological studies have indicated that the risk of being involved in a traffic accident increases only slightly at BAC levels of ≤0.04%,^[10]^ increases by about double around a BAC level of 0.05%, and increases exponentially starting at a BAC level of 0.10%.^[11]^ Therefore, for the purposes of this study, we decided to use a BAC level of 0.05% as a threshold for clinically meaningful driving impairment. As a BAC level of ≥0.10% can easily cause drunkenness, 4 BAC levels (0.00% [placebo], 0.025%, 0.05%, and 0.09%) will be set to calculate the SDLP regression curve. The hypothesis of this study is that SDLP will increase in accordance with BAC levels.

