### Participants

2.2

Healthy Japanese men were recruited through online advertisements and from Fukuoka Mirai Hospital. Because this is an exploratory study, the sample size was set to 24 participants in reference to the sample size of previous studies conducted to confirm the validity of a DS.^[6,12]^ The inclusion criteria are: age between 21 and 65 years; body mass index between 18.5 and 24.9 kg/m^2^; active-type aldehyde dehydrogenase (ALDH) gene polymorphism (ALDH 2∗1/∗1); alcohol consumption >2 days a month; able to drink a prespecified amount of alcohol in 30 minutes; possession of a driver's license and driving daily for >3 years; consistent sleeping pattern (wake up between 06:00 and 09:00 am, go to bed between 21:00 and 00:00 pm); no visual impairments; able to operate a DS with a full understanding of all DS tasks; judged by a physician as being able to participate; and able to provide written informed consent before the examination begins. The exclusion criteria are: having a disease recognized as being nonhealthy by a physician; a history of drug or food allergies; 3) serious allergic predispositions; 4) a history of stroke, head trauma, epilepsy, or malignant tumor; more than a 3-month history of sleep disorders, a medical history of sleep apnea syndrome or restless legs syndrome, or a history of hypersomnia such as narcolepsy; use of over-the-counter drugs within 1 week after starting the practice period; use of sedative hypnotics within 4 weeks after starting the practice period; experiencing more than a 6-hour time difference within 4 weeks after starting the practice period; irregular shift work and night shift work within 4 weeks after starting the practice period; experience using the same DS evaluation method as that used in the present study; a daily routine of alcohol consumption until sleep; unable to stop drinking from 2 days before until the day of the screening test, and from 2 days before hospitalization until discharge; smoking during hospitalization; donating blood within 12 weeks; use of prescription drugs within 4 weeks after starting the practice period; a diagnosis or history of alcoholism or drug dependency; positive result from a urine drug test during screening; unable or unwilling to comply with the study protocol; and judged unsuitable for participation by a physician. The discontinuance criteria are: noncompliance with the study protocol; experiencing adverse events that compel a physician or the participant himself/herself to cease participation in the trial; the participant chooses to discontinue the trial of their own volition; sliding off the track or have a large SDLP such as >60 cm during the practice period; and judged unsuitable for participation by a physician.

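### Setting SDLP outliers to missing, without limiting this to technical faults, is expected to pull the 0.05% vs 0% SDLP threshold downward, by an amount the protocol does not let one determine

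*Protocol article*

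**What the plan says.** Section 2.11 of the protocol article gives one sentence on data handling: "Evaluation items with incomplete data will be excluded from analysis, and outliers will be treated as missing values." It follows the description of the SDLP analysis and the secondary outcomes, and nothing exempts SDLP. No other section limits the rule. The only numerical SDLP limit, above 60 cm, is a discontinuance criterion for the practice period (section 2.2), not an outlier definition for the test periods.

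The purpose, in the Introduction, is to "set a clinically meaningful SDLP threshold as a main evaluation item based on the difference between SDLP" at 0.00% and 0.05% BAC. The estimate comes from section 2.11: "The predicted difference in SDLP between the BAC 0.05% and 0% groups will be calculated using a linear model." The Introduction adds that "4 BAC levels (0.00% [placebo], 0.025%, 0.05%, and 0.09%) will be set to calculate the SDLP regression curve" and that "The hypothesis of this study is that SDLP will increase in accordance with BAC levels."

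Section 2.9 lists as a secondary outcome the "total number of times the vehicle goes off of the course (course-outs"), so very poor driving is something the trial intends to record.

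**The concern.** Alcohol is given in this trial to raise SDLP. A very high SDLP at 0.05% or 0.09% may be a recording fault, but it may equally be the effect under study. The sentence in section 2.11 does not separate the two: once a value is called an outlier, it becomes missing. Missingness then depends on the value of the outcome and, through it, on BAC. A model that treats such values as ignorably missing will tend to give too shallow a slope.

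The 0.05% vs 0% difference is meant to become the yardstick for judging drug effects on driving. If it is too low, later studies are compared with a threshold that under-represents the drivers most affected by alcohol.

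**Working it through.** **No figure to reproduce.** The protocol gives no SDLP variance, outlier rule or power calculation; "the sample size was set to 24 participants in reference to the sample size of previous studies." The check therefore has two parts: the leverage of each BAC level in the estimator, and a simulation under stated assumptions.

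**1. Weights of the four BAC means.** Assume a straight line in nominal BAC (0, 0.025, 0.05, 0.09).
- Mean BAC = 0.165 / 4 = 0.04125.
- Sum of squared deviations = 0.00441875.
- Weight of each mean in 0.05 × slope = 0.05 × (BAC - 0.04125) / 0.00441875.
- Result: -0.467 (0%), -0.184 (0.025%), +0.099 (0.05%), +0.552 (0.09%).

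The level where extreme values are most expected has the largest weight.

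**2. Deleting one drive at 0.09%.** Removing one of 24 values that lies D above the mean lowers that mean by D/23. The prediction falls by 0.552 × D/23. For D = 10 cm this is 0.552 × 10/23 = 0.24 cm, and it scales with D. D is an assumption. In a model with participant effects, only the part of D specific to that drive counts; a participant's generally high SDLP drops out.

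**3. Simulation.** 24 participants × 4 levels = 96 drives, 4,000 runs per scenario, linear model with participant effects, threshold = 0.05 × slope. The assumed inputs are:
- A: baseline 30 cm, between-participant SD 6, within-participant SD 3, effect at 0.05% of 2.4 cm (the on-road figure in the Discussion), constant sensitivity to alcohol.
- B: as A, with right-skewed (lognormal, log-SD 0.8) sensitivity.
- C: baseline 35 cm, SDs 8 and 4, effect 5 cm, same skewed sensitivity.

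The dose-response is linear in all three. With every drive kept, the estimates are 2.40, 2.40 and 5.00 cm, equal to the true values. With outliers set to missing, the change is:

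| Assumed outlier rule | A | B | C |
|---|---|---|---|
| 3 SD, pooled | -0.5% | -4.0% | -6.6% |
| 2 SD, pooled | -5.9% | -13.2% | -16.4% |
| 1.5 IQR, pooled | -1.7% | -7.1% | -11.1% |
| 2 SD, within BAC level | -0.1% | -5.5% | -8.1% |
| 1.5 IQR, within BAC level | 0.0% | -4.0% | -7.0% |
| Above 60 cm | 0.0% | -1.9% | -15.5% |

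In centimetres, 2.40 falls to 2.08-2.35 in B, and 5.00 falls to 4.18-4.67 in C. With skewed sensitivity, removal depends on dose. Under the pooled 2-SD rule, 3.5% of drives are removed at 0% against 6.9% at 0.09% in B, and 3.0% against 8.9% in C.

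**4. Convex dose-response.** With skewed sensitivity the loss was 7% to 28% relative to the same linear fit on all drives. There, however, the linear fit itself overstates the 0.05% effect (3.96 against 2.4 cm, and 8.20 against 5 cm), so deletion partly offsets another error. These percentages are not bias against the truth and are left out of the headline range.

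**5. Incomplete drives.** SDLP is taken over 60 minutes (section 2.11), and a test may be stopped for an adverse event (section 2.12). If such stops are alcohol-related, they fall more often at higher BAC and their exclusion acts in the same direction. The documents give no rate, so no number is attached.

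**The case against.** The strongest reply is that the article does not define an outlier, and that a condensed article may leave the definition to an analysis plan that is not shown. If that plan meant only technical artefacts, the concern would largely disappear. This stands as a limit on the size. It does not remove the point, because the article itself fixes the consequence (the value becomes missing) and attaches no technical condition.

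A reader might infer that the plan certainly deletes the most impaired drives and shrinks the threshold by a large, known amount. The documents do not support that:
- A deleted drive 30 cm above its mean would cost 0.552 × 30/23 = 0.72 cm, which is 30% of the on-road 2.4 cm. But the 30 cm has no source, and the Discussion says simulators tend to give larger SDLP than real vehicles. Against an assumed simulator effect of 4.8 cm, the same shift is 15%.
- With log-SD 0.9 to 1.2 for sensitivity, simulated losses reach 12% to 27%. That puts the 97.5th-percentile participant at about 5.8 to 10.5 times the median sensitivity (exp(1.96 × 0.9) and exp(1.96 × 1.2)). Nothing in the documents supports such a spread, and the trial restricts genotype and BMI and scales the alcohol amount by body weight. At log-SD 0.5 the loss is 1% to 2%.

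A reader might also infer that an incomplete drive removes the participant, or that early stops must cluster at high BAC. The sentence excludes evaluation items, not participants. Simulator sickness and drowsiness, which section 2.10 anticipates, can also occur at 0%.

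Finally, the protocol says "Because this is an exploratory study", and course-outs and line crossings would still be counted. Both are true. The exploratory label explains the sample size; it does not make outcome-dependent deletion suitable for the estimate that becomes the threshold.

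**Conclusion.** The point holds as a matter of expected direction. Section 2.11 deletes outlying SDLP values in the analysis that yields the threshold, whatever their cause. High values are the hypothesised effect of alcohol, and the 0.09% level has the greatest leverage, so deletion is expected to lower the estimate.

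The size is illustrative: about 0% to -16% under a linear dose-response, depending on the outlier rule and on how skewed alcohol sensitivity is. It is near nil if only technical artefacts are removed, or if the rule works within BAC level and sensitivity is roughly constant; with skewed sensitivity, the within-level rules still lost 4% to 8%. All of this rests on assumed SDs, baselines, sensitivity distributions and outlier rules, and the weights assume nominal BAC. The effect of excluding incomplete drives is plausible but unquantified.

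**What to change.** Replace the sentence in section 2.11 with wording to this effect:
- All valid recorded SDLP values enter the primary analysis.
- A value is removed only for a documented technical fault, judged blind to BAC.
- A participant's other periods are retained, in a model that uses all available periods.
- Removals and incomplete drives are reported by BAC level.
- Extreme values are examined only in sensitivity analyses: log SDLP, a robust fit, or outlier exclusion.
- Partial drives also enter only a sensitivity analysis, as SDLP to the stopping time. They are flagged as not being the 60-minute measure, since they omit the time after the stop and may themselves understate impairment.

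The cost is a change of wording, a little more analysis work, and a somewhat larger residual variance in the primary model.

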### Adverse events

2.12

If any adverse events occur after the start of the practice period, depending on the severity, the test will be stopped based on a decision by the doctor or the participant himself/herself, and the problem will be treated appropriately. All adverse events will be reported at the end of the study and listed, but not aggregated or analyzed.

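### Section 2.12 rules out any adverse-event summary by BAC level, although events can stop drives and incomplete drives are excluded; a descriptive table by level would be a free improvement

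*Protocol article*

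**What the plan says.** Protocol article, section 2.12 (Adverse events): if an event occurs after the practice period begins, then depending on severity "the test will be stopped based on a decision by the doctor or the participant himself/herself". The same section closes with the reporting rule: "All adverse events will be reported at the end of the study and listed, but not aggregated or analyzed".

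Section 2.2 (Participants) also makes adverse events a ground for leaving the trial. It sets the size: "the sample size was set to 24 participants in reference to the sample size of previous studies".

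Section 2.11 (Statistical analysis) plans summary statistics of SDLP at each BAC level and of the difference from 0%. The main estimate follows: "The predicted difference in SDLP between the BAC 0.05% and 0% groups will be calculated using a linear model". On missing and extreme data it says: "Evaluation items with incomplete data will be excluded from analysis, and outliers will be treated as missing values".

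The Introduction gives the design points: "4 BAC levels (0.00% [placebo], 0.025%, 0.05%, and 0.09%) will be set to calculate the SDLP regression curve".

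**The concern.** The crossover gives each of the 24 participants every alcohol level in a randomised order. It therefore supplies a within-participant comparison of adverse events across levels, and the reporting rule declines to summarise it.

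The protocol treats tolerability as a live matter. The Introduction keeps the top level below 0.10% because of drunkenness, and section 2.5 asks for care because Asian populations generally tolerate less alcohol.

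Adverse events also bear on the main result. An event may stop a drive, a stopped drive is incomplete, and incomplete items leave the analysis. If that happens mostly at the highest level, and mostly to the most impaired participants, the fitted SDLP slope is too flat. The 0.05%-versus-0% threshold would then be too low. No planned output described in the article would tell a reader whether this happened and why.

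**Working it through.** The article gives no adverse-event rate, dropout rate, SD or effect size, so there is no figure of the plan's own to reproduce. The check has four steps.

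**1. Inputs.** 24 participants (section 2.2); four levels, 0, 0.025, 0.05 and 0.09% (Introduction); each participant takes all four (sections 2.1 and 2.3). Hence there are 24 planned drives per level.

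**2. Which level matters most for the slope.** Assume a straight line with participant effects, at nominal BAC.
- Mean BAC = (0 + 0.025 + 0.05 + 0.09)/4 = 0.04125.
- Squared deviations: 0.001702, 0.000264, 0.000077 and 0.002377; total 0.004419.
- Shares: 0% 38.5%, 0.025% 6.0%, 0.05% 1.7%, 0.09% 53.8%.

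A participant who loses only the 0.09% drive keeps the sum of squares of the other three levels, 2 × 0.025² = 0.00125. That is 0.00125/0.004419 = 28.3% of his slope information. With k such losses, the information left is 1 − 0.717k/24 and the standard error grows by the inverse square root of that.

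| 0.09% drives lost | Information left | SE increase |
|---|---|---|
| 2 | 94.0% | 3.1% |
| 4 | 88.0% | 6.6% |
| 6 | 82.1% | 10.4% |

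The loss of precision is modest. Bias from selective loss can be larger.

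**3. Illustration of the bias.** This simulation used 1,500 runs per setting and rests on assumptions, not on figures from the article. The true 0.05%-versus-0% difference is set to 1. The SD of participants' slopes (expressed on the scale of that difference) and the residual SD are both 0.5 or both 1.0. The participants with the largest observed rise from 0% to 0.09% lose the 0.09% drive.

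| 0.09% drives lost | Mean estimate, SDs 0.5 | Mean estimate, SDs 1.0 |
|---|---|---|
| 0 | 0.995 | 0.990 |
| 2 | 0.932 | 0.863 |
| 4 | 0.885 | 0.760 |
| 6 | 0.838 | 0.665 |

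This is a severe mechanism, because exactly the most affected participants are removed. If the lost drives were unrelated to SDLP, this bias would not arise.

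**4. What each output would reveal.**
- *Listing of events:* each event, one at a time. Counts by level only if the reader tallies them and the listing carries period or level.
- *Number of SDLP values per level:* probably part of the planned summary statistics, though the article does not name it. It would show a shortfall at 0.09%, but not whether drives were stopped by events or deleted as outliers.
- *Sickness and sleepiness questionnaires:* as section 2.6 is worded, the sickness questionnaire is given before and after the task on Day 1, which is the practice period. Sleepiness and mood are measured before the task. On that wording (Table 3 is not shown) there is no sickness measure after the drive at each BAC level.
- *Table by level with reasons:* counts of events and lost drives out of 24, separated by cause.

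Such counts are imprecise but usable for description. Exact 95% intervals are 0 to 14.2% for 0/24, 1.0 to 27.0% for 2/24, 4.7 to 37.4% for 4/24 and 9.8 to 46.7% for 6/24.

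**The case against.** The strongest reply is that nothing is lost. All events are to be reported and listed, and with 24 participants anyone can count them by level after unblinding. Nothing in the article says that the listing omits period, level or severity. This stands. A reader might infer that the trial cannot show tolerability by level, but the article supports only that no summary is planned.

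A second reply is that any bias in the slope comes from the exclusion rule in section 2.11. This also stands. A reader might infer that the adverse-event sentence itself biases the threshold, or that a table would cure the bias. Neither follows: the table leaves the analysed data unchanged. Nor does the article show that stopped drives would be those with the highest SDLP; a drive stopped for nausea need not be.

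A third reply is that alcohol here is a calibrator. The method intended for wider use is the simulator, adverse events are not a named outcome, and the study is exploratory in healthy men. Entry is limited to carriers of the active ALDH2 genotype who can drink the set amount. These facts lower the importance of the point and make a listing defensible.

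What remains is narrower. The rule excludes a simple summary that the design makes easy, and no other output described in the article gives the reasons for lost drives by level.

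**Conclusion.** The point holds as a minor one. The article expressly excludes an adverse-event summary by BAC level, while its own rules let events remove drives from the SDLP analysis. A descriptive table would make selective loss and its causes visible. It would not correct any resulting bias, and its absence does not invalidate the threshold.

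The 53.8% weight of the 0.09% level assumes a straight line at nominal BAC. It would differ if the measured BAC described in section 2.4 is the regressor. The shrinkage figures depend wholly on the assumed SDs and loss mechanism, and show direction and possible scale only. That the listing could be tallied assumes that it carries period or level. That a shortfall would be visible assumes that the number of values per level is reported.

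**What to change.** In section 2.12, replace the clause that bars aggregation and analysis with wording such as: adverse events will be listed and also tabulated descriptively by assigned BAC level, giving the number of participants with any event, by term and severity, and the number of drives stopped or excluded, with the reason, out of 24 per level. No formal test is needed.

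The cost is one extra table. It needs no new measurements, provided that the reason for each lost drive is recorded, and it changes no rule on stopping a test or on participants' care. The exclusion rule in section 2.11 is a separate matter that this change does not settle.

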### Ethics and dissemination

2.13

This study was registered at ClinicalTrials.gov (NCT 03572985) on June 28, 2018. The study protocol was approved by the Ethics Committee at Hakata Clinic (1747CP-3) and the Nagoya University Medical School Hospital Bioethics Review Committee (2010-0970-3), and the study has been being performed at Fukuoka Mirai Hospital. Informed consent was obtained from all study participants. For privacy protection, participants will be identified using an identification code. Information such as the participant's name and address will be managed only at the medical examination center and will not be provided to other organizations. If any necessary experimental data are provided to a joint research institution (sponsor and investigator), these will be carefully protected using only the participants’ identification codes and a corresponding table. The sponsor and investigator will have access to the final test data, and the final results will aim to be published in a journal article. The acquisition of informed consent, inclusion/exclusion criteria, participants’ eligibility, and occurrence of any adverse events will be confirmed by monitors from outside the testing agency. These monitors will ascertain whether the experiment is being carried out according to the approved procedure and confirm that the data storage method is appropriate. We will also set up an independent auditor from the testing department who evaluate whether the experiment complies with the protocol. All test-related data will be disclosed to the monitor or auditor for the purposes of conducting a survey. The findings will be aimed to be published in peer-reviewed journals and presented at local, national, and international conferences to publicize and explain the research to key audiences.

